### ***Long term Neuropsychological impairment***

- Beck's Depression Inventory (BDI-II)(73): this instrument screens for depression using criteria consistent with the Diagnostic and Statistical Manual of Mental Disorders-Fourth Edition. Higher scores (range, 0-63) indicate more depressive symptoms. Based on testing in psychiatric outpatients, depression symptoms severity is classified as minimal score (score 0-13), mild (score 14-19), moderate (score 20-28) and severe (score 29-63). The BDI-II will be performed at hospital discharge and 6 months after ICU discharge.
- Repeatable Battery for the Assessment of Neuropsychological Status (RBANS)(74-76): The RBANS is a comprehensive and validated neuropsychometric battery for the evaluation of global cognition, including individual domains of immediate and delayed memory, attention, visuospatial construction and language. The RBANS will be performed at hospital discharge and 6 months after ICU discharge.

### ***g. Sample size and statistical analysis***

According to a previous study, which measured sleep with PSG (63), and other studies, which have described sleep architecture in the ICU (3-7), we estimate that the N3 stage time in our study population will be 7 minutes with a SD of 9 minutes. We considered that a 50% improvement in N3 stage time would be both, clinically relevant and realistic. With a power of 80% and with alpha of 5%, we calculated that a sample size of 56 patients is required to demonstrate statistically significant differences.

General statistical analysis will be performed according to intention to treat. Baseline characteristics will be reported using mean values  $\pm$  standard deviation (SD), or median (p25-75) and proportions where

appropriate. The use of parametric vs non-parametric tests will be decided according to data distribution and the fulfillment or not of normality assumptions. Specific statistical analysis for comparisons between groups will be performed by Student's-t test or Mann-Whitney U-test for continuous variables, and by chi-square for proportions. Changes along time will be analyzed by one-way (repeated-measures) analysis of variance (ANOVA) or Friedman test. Interactions between groups and time we will assessed with two-way repeated-measures ANOVA. All statistical calculations will be performed using Stata Statistical Software, Release 15.1 (College Station, TX). A probability value (p-value) of less than 0.05 will be considered as statistically significant.

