## **5. Relevance of the present study**

Although several factors have been associated to sleep disturbances in ICU patients, a recommendation about the best strategy to improve sleep and re-establish the circadian rhythm has not yet been made. As sleep deprivation in ICU may contribute to relevant clinical outcomes, effective strategies to improve sleep are worth to be investigated. We propose an interdisciplinary and pragmatic approach which targets different environmental factors, and which integrates experts from different fields. Although the concepts of dynamic light and sound masking are well known, our proposal includes the local design of solutions based on these concepts. We also chose to use the highest standard for sleep measurements (PSG), which has been one of the major limitations of previous research in this field.

We expect that our intervention will be effective to improve sleep. Although this study is underpowered to study potential impacts of the strategy on mortality or ICU length of stay, if the intervention proves to be effective in improving sleep, a larger scale study could follow. But even if the intervention proves not to be effective, the data collected about sleep and about long-term neuropsychologic outcomes in our ICU population will be highly relevant to advance our understanding about the relation between these variables, and for the planning of future studies.

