## **III. Methodology**

### **a. Study design**

Prospective, parallel-group, randomized trial in critically ill patients. Our project will follow the CONSORT (64) guidelines for this class of studies.

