#### **d. Randomization**

Patients who meet criteria and who are hospitalized in a modified ICU room will be invited to participate in the study. However, if a patient meets criteria, but is placed in another room, he/she can be transferred to any of the modified rooms if any of them is free. Once the Informed Consent signature is obtained, patients will be randomized to receive a multifaceted intervention of environmental control in the ICU (dynamic light therapy, auditory masking, and rationalization of ICU nocturnal patient care activities) (intervention group) or standard care (control group). The randomization sequence will be generated by a computer program with an allocation 1:1. Due to the type of intervention under study the patient and the research team can't be blinded to the group assignment. Nonetheless, statisticians and the researchers responsible for analysis of PSG and actigraphy, as well as those performing long-term outcome assessments will be blinded to the group allocation.

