#### **IV. Work plan**

We request funding for a 4-year study because during the first year of study we will implement the intervention in the ICU. We will recruit 56 patients, and considering the admission database of our ICU (in our ICU 1600 patients are admitted per year), we estimate that 2 - 3 patients could be included per month. We require at least 24 months of continuous screening to meet this target and complete the follow-up, starting inclusion by the 8th month of the project, and finishing the 6th month of the four year.

| Aim or task                                                                                                                                                    | Year1
Sem1 | Year1
Sem2 | Year2
Sem1 | Year2
Sem2 | Year3
Sem1 | Year3
Sem2 | Year4
Sem1 | Year4
Sem2 |
|-----------------------------------------------------------------------------------------------------------------------------------------------------------------------|-----------------------|-----------------------|-----------------------|-----------------------|-----------------------|-----------------------|-----------------------|-----------------------|
| Purchase of equipment and material                                                                                                                                    | X                     | X                     | X                     |                       |                       |                       |                       |                       |
| Implementation of intervention (modifications of the 4 ICU rooms), development of protocol for the nocturnal patients care activities, neasurements and readjustments | X                     | X                     | X                     |                       |                       |                       |                       |                       |
| Pilot                                                                                                                                                                 |                       | X                     |                       |                       |                       |                       |                       |                       |

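### On the protocol's own inputs, 56 patients give about 30% power for a 50% gain in N3 time (two-sided t-test), not the stated 80%

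*Protocol*

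**What the plan says.** All inputs stand in the Protocol.

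- **Control mean and SD** (section g, Sample size and statistical analysis): "we estimate that the N3 stage time in our study population will be 7 minutes with a SD of 9 minutes".
- **Target effect** (same section): "We considered that a 50% improvement in N3 stage time would be both, clinically relevant and realistic".
- **Error rates** (same section): "With a power of 80% and with alpha of 5" per cent. Sidedness is not given.
- **Result** (same section): "we calculated that a sample size of 56 patients is required to demonstrate statistically significant differences".
- **56 is the total** (section IV, Work plan): "We will recruit 56 patients".
- **Design** (section a, Study design): "Prospective, parallel-group, randomized trial in critically ill patients".
- **Allocation** (section d, Randomization): "The randomization sequence will be generated by a computer program with an allocation 1:1".

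Section g compares the groups by Student's t-test or the Mann-Whitney test. The section on quantitative assessment of sleep provides for one polysomnography (PSG) per patient, on day 3, so there is no baseline N3 value. The primary outcome covers N3 time and REM time. Section g gives sample-size assumptions for N3 only.

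**The concern.** A 3.5 min difference against an SD of 9 min is a standardised effect of about 0.39. Two independent groups of 28 are far too small to detect that with 80% power, so the stated number and the stated power cannot both be right.

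The stake is the reading of the primary outcome. If the true gain is exactly the one the protocol calls relevant and realistic, the t-test would miss it about 7 times in 10. Section I.5 (Relevance of the present study) concedes low power for mortality and ICU length of stay only, so a reader will take the 80% for sleep at face value. A funder or ethics board would do the same.

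**Working it through.** **Inputs.** Control mean 7 min; SD 9 min, taken as equal in both arms; difference 0.50 × 7 = 3.5 min; standardised effect 3.5/9 = 0.389; alpha 5%; power 80%; 56/2 = 28 per arm.

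**1. Trying to reproduce 56.** For two independent means with 1:1 allocation, n per arm = 2 × SD² × (z_alpha + z_power)² / difference².

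- Two-sided: 2 × 81 × (1.960 + 0.842)² / 12.25 = 103.8, so 104 per arm (208 in total). The exact t-test calculation gives 104.8, so 105 per arm (210 in total).
- One-sided: 82 per arm by the normal approximation; the exact t-test gives 82.4, so 83 per arm (166 in total).

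Neither gives 56 in total or 56 per arm.

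**2. Power with 28 per arm.** Standard error = 9 × √(2/28) = 2.405 min, and 3.5/2.405 = 1.455.

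- Two-sided, normal approximation: Φ(1.455 − 1.960) = 30.7%; exact t-test 29.8%.
- One-sided, normal approximation: Φ(1.455 − 1.645) = 42.5%; exact t-test 41.8%.

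**3. What 28 per arm can detect with 80% power.** (1.960 + 0.842) × 2.405 = 6.74 min; exact t-test 6.86 min. As a share of 7 min, 6.86/7 = 98%. Alternatively, for 3.5 min the SD would have to be about 4.6 min, roughly half the stated 9.

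**4. Precision.** Expected 95% CI half-width = t(0.975; 54 df) × 2.405 = 2.005 × 2.405 = 4.82 min, wider than the 3.5 min target. The upper limit falls below 3.5 min only if the observed difference is below 3.5 − 4.82 = −1.3 min, that is, if N3 time is shorter on the intervention.

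**5. Other readings of 56.**

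| Reading | Result | Why it does not rescue the figure |
|---|---|---|
| 56 per arm | power 53% two-sided, 66% one-sided | the work plan makes 56 the total, and power is still below 80% |
| One-sample or paired formula, 3.5 min | 52 (normal) or 54 (t) | independent groups, one PSG per patient |
| Two-arm formula, 7 min (a doubling) | 26 or 27 per arm, 52 to 54 in total | section g states 50% |
| Log-normal scale, same coefficient of variation | 94 per arm; power 34% with 28 per arm | still far from 56 |
| SD rising with the mean (9 and 13.5 min) | power about 21% with 28 per arm | worse |

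The second and third readings come close to 56 but do not equal it. The source of the figure is unknown.

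**6. Loss of recordings.** Section g calculates 56 and the work plan recruits 56. If 15% of day-3 recordings were lost (an assumption; the Protocol gives no rate), 28 × 0.85 ≈ 24 per arm remain and the exact two-sided power is 26%.

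**The case against.** **The 30% depends on the test and on equal SDs.** This stands as a qualification. Sidedness is unstated, and section g also allows the Mann-Whitney test. A non-negative variable with mean 7 and SD 9 is strongly skewed, and under skew that test can behave quite differently. Simulations with assumed shapes, 28 per arm and a two-sided 5% level gave:

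- proportional 50% gain: about 15% power (gamma) and about 29 to 31% (log-normal);
- equal SDs in both arms: about 61% (gamma);
- pure 3.5 min shift: about 73% (gamma) to 85% (log-normal).

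So one assumed case does pass 80%. It requires every treated patient to gain the same 3.5 min, which fits poorly with the Protocol's own statement (section I.2, Sleep in critical illness) that N3 may be absent in these patients. The proportional model is closest to a 50% improvement and does no better than about 30%. Section g states only a mean and an SD and mentions no such model.

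**Section I.5 might be read as claiming that a null result would prove inefficacy.** The words "But even if the intervention proves not to be effective" invite that, but the sentence goes on to say that the data would still be valuable. It sets no decision rule and claims no proof of absence, so the passage needs no rewrite. Nor would an upper limit below 3.5 min rule out any effect at all; it would exclude only gains of 3.5 min or more.

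**A reader might infer that the trial must enrol 210.** The documents do not support that as a simple correction. At the work plan's 2 to 3 patients per month, 210 would take 210/3 = 70 to 210/2 = 105 months. The plan allows about 34 months (month 8 to month 42), with four modified rooms.

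**Lost recordings are a separate matter.** Agreed: the missing allowance is secondary and is not the arithmetic error.

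**Conclusion.** The sample-size statement is wrong as written. For N3 time, the stated inputs and design give about 30% power two-sided (about 42% one-sided) rather than 80%, and the stated power would need about 105 evaluable patients per arm two-sided, against 28. These figures assume a two-sample t-test, a common SD of 9 min and no missing recordings. No two-arm calculation tried with the stated effect and SD, including the one-sided test and 56 read as per arm, reproduces 56.

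The conclusion is limited to N3 time. Nothing can be said about power for REM time, the other part of the primary outcome, because no assumptions are given for it. Because the error is in a figure that the Protocol itself states, a separate analysis plan would not remove it.

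**What to change.** In Protocol section g, replace the 80% claim with wording such as:

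> For N3 time, with 28 evaluable patients per arm, SD 9 min and a two-sided 5% t-test, the trial has 80% power for a difference of about 6.9 min (roughly a doubling) and about 30% power for 3.5 min. Any loss of day-3 PSG recordings lowers this further (for example, to about 26% for 3.5 min with 24 per arm, an assumed loss). The expected 95% confidence interval half-width is about 4.8 min, so a non-significant result would not by itself exclude a gain of 3.5 min. The estimated difference will be reported with its 95% confidence interval.

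This also settles the sidedness. Design, recruitment target and section I.5 can stay as they are. The cost is a less favourable stated power, visible to the funder and the ethics board. Raising enrolment to about 210 evaluable patients is a different decision with a large feasibility cost and is not part of this fix.

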### **Specific goals**

1. To compare the effects of the use a multifaceted intervention of environmental control in the ICU versus standard care, in quantity and quality of sleep by PSG and actigraphy, and by questionnaires, during the whole stay in ICU or up to day 30, and at hospital discharge and 6 months after ICU discharge.
2. To compare the effects of the use a multifaceted intervention of environmental control in ICU versus standard care, in the oscillation of plasma concentrations of Melatonin and Cortisol during the ICU at days 1 and 3 after randomization.
3. To compare the acute effects of the use a multifaceted intervention of environmental control in the ICU versus standard care, on prevalence and duration of delirium during ICU stay.
4. To compare the effects of the use a multifaceted intervention of environmental control in the ICU versus standard care, in neuropsychological impairment (depressive symptoms and cognitive impairment) at 6 months after ICU discharge.

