### **Secondary outcomes**

- 1) Total time of sleep assessed by actigraphy
- 2) Sleep quality assessed by questionnaires (RCSQ and PSQI)
- 2) Circadian timing: Oscillation of plasma concentration of Melatonin and Cortisol
- 3) ICU delirium (prevalence and duration of delirium in ICU) by Confusion Assessment Method for the ICU (CAM-ICU)
- 4) Neuropsychological impairment (depressive symptoms and cognitive impairment) at 6 months post ICU discharge by cognitive testing and instrument screens of depression

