#### **f. Study variables**

- 1. Baseline parameters to be collected:** At the time of enrolment, information collected on each patient will include the following: patient demographics, dates of hospital and ICU admission, illness severity according to the Acute Physiology (APACHE II), Chronic Health Evaluation II and Sequential Organ Failure Assessment Score (SOFA), comorbidities according to the Charlson Comorbidity Index, admission diagnoses, and pre-existing neuropsychological impairment.
- 2. Repeated assessments to be performed during the study protocol:** During the course of each patient's stay in the ICU data will be collected on: Sequential Organ Failure Assessment Score (SOFA), Partial pressure of oxygen (PaO2)/Fraction of inspired oxygen (FiO2), daily arterial pressure and minimum glycemia value obtained, daily doses of medications. Use of hemodialysis and vasopressors, mechanical ventilation duration and ICU/Hospital length of stay data will be collected also. All patients will undergo a standardized follow-up immediately prior to hospital discharge and at 6 months later. At 6 months patients will attend to a follow-up visit, and if they are unable to attend they will be visited at home.

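### The discharge and 6-month scores exist only for survivors, so the blanket intention-to-treat statement does not hold for them; label those comparisons as conditional on survival

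*Protocol*

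**What the plan says.** Protocol section g (Sample size and statistical analysis) sets one principle for the whole analysis: "General statistical analysis will be performed according to intention to treat". No outcome is excepted. The group comparisons are fixed there too: "Specific statistical analysis for comparisons between groups will be performed by Student's-t test or Mann-Whitney U-test for continuous variables", chi-square for proportions, and "Interactions between groups and time we will assessed with two-way repeated-measures ANOVA".

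Goal 4 under Specific goals compares the arms "in neuropsychological impairment (depressive symptoms and cognitive impairment) at 6 months after ICU discharge", and the matching secondary outcome is "Neuropsychological impairment (depressive symptoms and cognitive impairment) at 6 months post ICU discharge by cognitive testing and instrument screens of depression". The section on long-term neuropsychological impairment sets the time points: "The BDI-II will be performed at hospital discharge and 6 months after ICU discharge" and "The RBANS will be performed at hospital discharge and 6 months after ICU discharge". PSQI is completed at 6 months and belongs to goal 1.

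Section f (Study variables) says "All patients will undergo a standardized follow-up immediately prior to hospital discharge and at 6 months later", with a home visit for those who cannot attend. The exclusion criteria remove patients with no fixed address and those whose pre-existing illness limits life expectancy to 6 months or less. The document does not rank or score death, and does not describe goal 4 as conditional on survival.

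**The concern.** Deaths have to be expected. Entry requires at least 72 hours of invasive ventilation. The background links poor sleep in critical illness to mortality, and the section on the relevance of the study names mortality as something the strategy might affect, although the trial is too small to study it. The safeguards in the text (home visits and the two exclusions) do not cover death from the acute illness.

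A patient who dies before an assessment has no BDI-II, RBANS or PSQI value, so a t-test, a Mann-Whitney test or a repeated-measures ANOVA on those scores drops that patient. Survival is settled after randomisation. If the arms differ in how many patients die, or in which patients die, the survivors are no longer two randomised groups. An arm that keeps frailer patients alive can then look worse on mood or cognition without any effect on either. A reader told that the analysis is by intention to treat would not look for this.

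**Working it through.** **1. Inputs.** The plan's total is 56 with 1:1 allocation, so 56/2 = 28 per arm. That total was set for N3 time (mean 7 min, SD 9 min, 50% improvement = 3.5 min). The usual two-sided two-group formula, 2 × (1.96 + 0.84)² × (9/3.5)², gives 104 per arm or 208 in total, so 56 is not reproduced. That is a separate matter; only the 28 per arm is used here. The protocol gives no mortality rate, and no correlation between risk of death and later scores. Both are assumptions below.

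**2. Patients with a score.** Per arm this is 28 × (1 − m), where m is mortality: 23.8 at 15%, 22.4 at 20%, 19.6 at 30% and 16.8 at 40%.

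**3. Shift with no true effect.** Take a score with SD 1 on which high is good (reverse the sign for BDI-II), correlated ρ with a normal robustness variable, and let the least robust fraction m of each arm die. Then

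E[score | alive] = ρ × φ(z_m)/(1 − m)

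The factor φ(z_m)/(1 − m) is 0.274 at 15%, 0.350 at 20%, 0.497 at 30% and 0.644 at 40%. The difference between arms is therefore

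- 30% v 15% deaths: ρ × (0.497 − 0.274) = ρ × 0.222 (from unrounded factors)
- 40% v 20% deaths: ρ × (0.644 − 0.350) = ρ × 0.294

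The standard error, taking SD 1, is √[1/(28(1 − m₁)) + 1/(28(1 − m₂))]:

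- 30% v 15%: √(1/19.6 + 1/23.8) = 0.305
- 40% v 20%: √(1/16.8 + 1/22.4) = 0.323

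| Deaths | ρ = 0.3 | ρ = 0.5 | ρ = 0.7 |
|---|---|---|---|
| 30% v 15% | 0.07 SD (0.22 SE) | 0.11 SD (0.36 SE) | 0.16 SD (0.51 SE) |
| 40% v 20% | 0.09 SD (0.27 SE) | 0.15 SD (0.46 SE) | 0.21 SD (0.64 SE) |

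Each shift favours the arm with more deaths. It is zero if ρ = 0 or if mortality is equal in this model.

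**4. Effect on the test.** A simulation used 28 randomised per arm, no true effect, a two-sided 5% t-test on survivors and 10,000 runs per setting. With 20% deaths in both arms (ρ = 0.5), a given arm is declared better in 2.4% of trials, against a nominal 2.5%. With 20% v 40%, the arm with more deaths is declared better in 6.6% (ρ = 0.5) or 10.4% (ρ = 0.7).

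**5. Scale.** With 28 scored patients per arm, the difference detectable with 80% power is 0.76 SD. The shifts in step 3 are about 9% (0.067/0.762) to 27% (0.206/0.762) of that.

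**The case against.** The strongest reply is that handling of deaths at secondary time points normally belongs in the SAP, which is not shown, and that intention to treat may mean only analysis by allocated arm, which a comparison of obtained scores satisfies. The outcomes are also framed as post-intensive-care impairment, so living patients may be implied and the promise to follow all patients may be loose wording. Part of this stands: an SAP could add a rule, and the absence of one is not the finding. What remains is that the protocol makes an unqualified claim and fixes tests which, for these scores, can use only survivors. An SAP rule would leave that claim overstated.

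The second reply is that the shift is modest and assumed. That stands. The mortality rates and correlations are not in the documents, the cases shown have mortality doubling between arms, and at a correlation of 0.3 the shift is below 0.3 SE.

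The third is that ranking death as worst turns a question about mood, cognition or sleep into one partly about mortality. With equal true mortality of 15% to 40%, the arms would still differ by at least 4 deaths with probability 0.19 to 0.34, and that noise would enter every ranked score. This also stands, and it is why the ranked analysis should not be the main one.

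A reader might go further and infer that the sign of goal 4 depends on how the dead are counted, for example as unimpaired in a proportion of all randomised patients. The protocol states no such denominator and gives no impairment cut-off for RBANS, so that reversal would come from an analysis the plan does not contain. A reader might also infer that unblinded staff could pick a convenient rule. The Randomization section blinds statisticians and long-term assessors, which counts against that.

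**Conclusion.** The point holds in limited form. For BDI-II and RBANS at hospital discharge and 6 months, and for PSQI at 6 months, the planned tests give a survivors-only comparison that the blanket intention-to-treat statement misdescribes. The comparison can favour the arm with more deaths, by about 0.07 to 0.21 SD (0.2 to 0.6 SE) under the assumed mortality gaps and correlations of 0.3 to 0.7. Bias needs unequal mortality, or different kinds of patients dying in each arm, together with a link between risk of death and score. The documents do not show that it will occur. The affected outcomes are secondary; the point does not concern the day-3 polysomnography outcome.

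**What to change.** In section g:

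- State that comparisons of BDI-II, RBANS and PSQI are among survivors and conditional on survival, not intention to treat, and report deaths by arm beside them.
- Prespecify one sensitivity analysis per score in all randomised patients, using the Mann-Whitney test already named, with death before the assessment ranked worst.
- For any impairment proportion, use survivors as the denominator or count being alive without impairment as the good outcome. Never count the dead as unimpaired.
- Word the goal 4 conclusion as applying to survivors, and say so if the sensitivity analysis differs.

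In section f, change the follow-up sentence to refer to all surviving patients, and list vital status at each assessment among the variables, since the ranked analysis needs it.

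The cost is wording, one recorded item and one extra analysis per score. The ranked result mixes death with function, so it serves as a sensitivity analysis only. Survivors without a score remain an ordinary missing-data matter for the SAP.

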Major factors for sleep deprivation in critically ill patients are the type and severity of underlying illness, the pathophysiology of the acute illness, pain (from procedures or the underlying condition), and stress/anxiety (6). Mechanical ventilation (MV) may also contribute to sleep disruption in critically ill patients. Sleep in mechanically ventilated patients is highly fragmented (6-12). However, studies that have examined PSG in these patients have observed the same patterns of sleep architecture as in patients without MV (9-12). Similarly, several commonly used ICU medications, including vasopressors, antibiotics, sedatives, opioids, and analgesics, may have profound effects on sleep quantity and quality (6,9-12). Although these factors related to patients' condition play a large role in sleep disruption, they are difficult to modify. However, factors associated to the ICU environment have also been reported to have a major role in sleep disturbance (e.g, lighting, noise, patient care activities), but they can be modified by changes in ICU design and culture (20).

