### **Primary outcome**

- 1) Sleep quantity (time in slow wave sleep-N3 and time in Rapid eye movement-REM) assessed by PSG at day 3

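### The primary N3 and REM comparison is fixed as unadjusted although enrolment severity scores are collected: a valid test that may give up a modest amount of precision

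*Protocol*

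**What the plan says.** The primary outcome is "Sleep quantity (time in slow wave sleep-N3 and time in Rapid eye movement-REM) assessed by PSG at day 3". The protocol's section on quantitative assessment of sleep schedules a single PSG per patient, on day 3, so there is no baseline PSG value.

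Section g (Sample size and statistical analysis) states that "Specific statistical analysis for comparisons between groups will be performed by" Student's t-test or the Mann-Whitney U-test when the variable is continuous, chosen by distribution. The other models named there, repeated-measures ANOVA and Friedman, concern change over time and cannot apply to an outcome measured once. Baseline characteristics appear in that section only as descriptive summaries.

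The background section on sleep in critical illness says: "Major factors for sleep deprivation in critically ill patients are the type and severity of underlying illness", and goes on to list other patient factors. Section f (Study variables) collects APACHE II and SOFA at enrolment. Section d (Randomization) says "The randomization sequence will be generated by a computer program with an allocation 1:1" and names no stratification factor.

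For planning, "we estimate that the N3 stage time in our study population will be 7 minutes with a SD of 9 minutes", and "We considered that a 50% improvement in N3 stage time would be both, clinically relevant and realistic". With 80% power and 5% alpha the protocol arrives at 56 patients.

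**The concern.** The protocol identifies a prognostic factor, measures it before treatment can affect it, and then fixes a primary comparison that cannot use it. There is no baseline PSG to adjust for and no stated stratum to balance severity. The analysis is therefore the only place left where severity could be taken into account.

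If severity does predict N3 and REM time, that part of the between-patient variation stays in the error term. The trial then has a wider interval than its own data would allow. In a trial of 56 patients that is worth avoiding if the remedy is cheap. Naming the covariate in advance also closes off a later, data-driven decision to adjust should severity turn out uneven between the arms.

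**Working it through.** **Inputs from the protocol:** control mean N3 time 7 min; SD 9 min; 50% improvement, so the difference is 0.5 × 7 = 3.5 min; 56 patients at 1:1, so 28 per arm; alpha 5%. Sidedness is not stated, and two-sided is assumed. The within-arm correlation r between severity score and N3 time is not given, so it is varied.

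**Step 1, the protocol's own figure.** n per arm = 2(1.960 + 0.842)² × 9² / 3.5² = 2 × 7.85 × 81 / 12.25 ≈ 104, or 208 in total. The exact t-test gives 105 per arm (210). One-sided 5% gives 82 per arm (164). The stated 56 is not reproduced.

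**Step 2, unadjusted power with 28 per arm.** SE = 9 × √(2/28) = 2.41 min. Noncentrality = 3.5 / 2.405 = 1.455 on 54 df. Power from the noncentral t is 29.8%.

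**Step 3, power adjusted for one covariate.** The residual SD becomes 9√(1 − r²). Estimating the covariate costs one degree of freedom (53 left) and inflates the variance by an expected factor of 1 + 1/52. So SE = 9 × √(1 − r²) × √(2/28) × √(53/52).

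| r (assumed) | Outcome variance explained | SE (min) | Power |
|---|---|---|---|
| 0 | 0% | 2.43 | 29.3% |
| 0.1 | 1% | 2.42 | 29.6% |
| 0.2 | 4% | 2.38 | 30.3% |
| 0.3 | 9% | 2.32 | 31.7% |
| 0.4 | 16% | 2.23 | 33.9% |
| 0.5 | 25% | 2.10 | 37.2% |

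The SE breaks even where 1 − r² = 52/53, that is, r ≈ 0.14. A second covariate (52 df, inflation 1 + 2/51) would lower power to 31.2%, 33.3% and 36.6% at a joint correlation of 0.3, 0.4 and 0.5.

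**Step 4, form of the adjusted model.** A non-negative time with mean 7 and SD 9 must be strongly right-skewed. Take a lognormal with those moments as an illustration. The log-scale SD is √ln(1 + 81/49) = 0.99, and the median is 7 / √(1 + 81/49) = 4.3 min. In simulations of this kind with 28 per arm, a linear model on raw minutes had about 22–26% power. The Mann-Whitney test, which the protocol would probably choose for such data, had about 29–31%. Rank-based adjustment kept the Mann-Whitney power and added roughly 1 to 8 points, depending on the correlation. Adjusting on raw minutes could therefore lose more than it gains.

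**The case against.** The strongest reply is that nothing here is an error. Under randomisation the unadjusted comparison is valid, choice of covariates is often left to a statistical analysis plan, and the documents never show that APACHE II or SOFA predicts N3 or REM minutes. The background sentence concerns sleep deprivation in ICU patients generally. The entry criteria (at least 72 hours of ventilation, no or light sedation) may narrow the severity range, and a floor near zero in N3 time may weaken any correlation.

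Most of this stands, and it limits the point to a refinement. The deferral argument does not: section g itself names the tests, so the unadjusted comparison is a stated choice and not an omitted detail.

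A reader might go further and infer that chance imbalance in severity biases the result. With 28 per arm, a difference above 0.3 SD in any given baseline score has about a 26% chance (0.3 / √(2/28) = 1.12 standard errors). But that is true of every baseline variable, and the test's standard error already covers it. At r = 0.3, such an imbalance shifts the N3 difference by 0.3 × 0.3 × 9 = 0.8 min, against an SE of 2.4 min.

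Nor does the protocol say that allocation is simple. It gives only a computer-generated 1:1 sequence and is silent on blocking. It also gives no basis for adding age as a covariate, since no passage links age to N3 or REM time.

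**Conclusion.** The point holds as a minor matter of efficiency. The protocol commits to an unadjusted primary comparison while holding a pre-treatment measure of a factor that it calls major. The cost is precision only.

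On the protocol's inputs, and assuming a two-sided test, the gain from one severity score is 0.5 points of power at r = 0.2 (30.3% against 29.8%), 1.9 at 0.3, 4.1 at 0.4 and 7.4 at 0.5. At r of about 0.1 there is none. The documents do not show where in that range r lies. These figures use the normal-theory calculation. With skewed times the direction is the same, provided that the adjusted analysis is rank-based or on a suitable transformed scale.

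It would be wrong to conclude that adjustment rescues the design. Even at r = 0.5 power stays below 40%. The shortfall comes from the sample-size calculation, which is a separate and larger fault.

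**What to change.** In section g, prespecify that the primary between-group comparison of N3 time, and likewise of REM time, is adjusted for one enrolment severity score. Name APACHE II or SOFA in advance. Use a form that suits skewed times with zeros: rank-based ANCOVA, or ANCOVA on a prespecified transformation that accepts zeros. Report the arm difference in minutes with a bootstrap interval, so that the result stays on the scale used for planning. Keep the unadjusted test as a supportive analysis.

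The cost is a sentence or two and no new data. If severity is not prognostic, the price is one degree of freedom and just under half a point of power (29.3% against 29.8%). A rank-based or transformed test and an interval in minutes can disagree near the significance threshold, so the text should say which one decides. The sample-size statement needs its own correction.
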